**Fig. 1 Fig1:**
[figure not shown]
Schematic Representation of the Randomized Controlled Trial

### Participants

A power analysis was performed based on the Penn State Worry Questionnaire (PSWQ [39]), which is traditionally used as the primary measure of change in studies of CBT for GAD with older adults. Assuming an effect size of .65 (difference in standard deviations between the scores of the treatment group and the wait-list group with telephone support, based on the work of other researchers [41] and a conservative estimate), an alpha threshold of .05 and power of .80, 90 participants are required (45 in each group). In anticipation of an estimated 30% drop-out rate based on previous work [41], a total of 130 people will be admitted to the study (accepted for treatment) in order to obtain the required number of 90. The maximum proportion of participants with a diagnosis of subthreshold GAD will be set at 40% of the sample. This percentage is similar to that in the study by Jones et al. [25] and reflects the priority given to GAD.

In order to be included, interested individuals will have to (a) be 60 years of age or older, (b) meet Diagnostic and Statistical Manual of Mental Disorder fifth edition (DSM-5 [1]) criteria for primary threshold or subthreshold GAD, (c) be able to read and speak French and to use the telephone without difficulty, and (d) if an anxiety medication is used, commit to maintaining the type of medication or dose during 8 weeks prior to treatment and during the protocol. Criteria for subthreshold GAD are based partly on the work of Miloyan et al. [4] and are as follows: 1) anxiety and excessive worries (expectation with apprehension) concerning several situations or activities; 2) anxiety and worries occurring most of the time; 3) anxiety and worries for a period of at least 6 months; 4) presence of one or two of the following: a) difficulty controlling worries; b) at least 3 of the following symptoms: restlessness or feeling keyed up or on edge, being easily fatigued, difficulty concentrating or mind going blank, irritability, muscle tension, sleep disturbance; c) significant impairment and distress related to worries and anxiety; 5) the subject of worries and anxiety is not better explained by another mental disorder. Participants with another disorder will be eligible if the interference associated with their comorbid disorder is not a contraindication to an initial therapeutic approach targeting generalized anxiety or if their comorbid disorder does not require an immediate intervention. The following exclusion criteria will be used during recruitment since they are associated with variations in the level of anxiety or to difficulties in adherence to treatment: (1) a disabling physical disorder that is not adequately controlled (e.g., acute heart disease, recent stroke), (2) the presence of a substance use disorder, (3) presenting a bipolar disorder or symptoms of a psychotic disorder, (4) having significant cognitive impairment (score lower than 22 on the Telephone version of the Mini-Mental State Examination (T-MMSE [42]), (5) currently receiving or having received psychotherapy for worries or anxiety over the last 6 months. Withdrawal of a participant admitted to the study will be made at the participant’s request or if an unforeseen condition prevents him or her from continuing to participate in the study or benefiting from the treatment. In the case of a withdrawal, the participant will be asked to answer the measurement instruments one last time. For all participants, a form will be completed by the site’s professional research assistant indicating whether the protocol was followed and, if not, why not.

Recruitment will be done with a continuous, targeted and diversified campaign (e.g., posters in institutions attended by older adults, articles in newsletters, magazines, and regional newspapers, older person’ awareness conferences, media interviews, on the Internet). The three study sites are located in three administrative regions of the province of Quebec, Canada, with a total population of nearly 800,000 people aged 60 and over (Capitale-nationale: 221,766; Montréal: 457,370; Estrie: 102,072) [43]. This population is sufficient for recruiting the sample. Individuals living in other administrative regions will be also eligible.

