### Data management and analysis

The principal investigators (PL, PG, and SG) will have access to all trial data. To protect the identity of participants and confidentiality of information, participants will be identified by a code number. Data obtained by paper questionnaires will be kept in a secure file. Data in electronic format will be kept on a secure server accessible to the research team only. Research assistants will double-entry data in paper format in order to detect and correct data entry errors. Data obtained from online questionnaires will be added to the data files.

SPSS for Windows will be used for statistical analyses. Missing data will be handled using multiple imputation. Descriptive analyses of study variables will be carried out. Analyses will follow intention-to-treat principles (i.e., data from all participants included in the study will be analyzed according to the randomization scheme). The pre- and post-treatment data will be used to compare the experimental and control groups. Repeated measures analysis of variance (ANOVA) will be performed on most outcome measures. Simple effects for group and time and group by time interactions will be analysed. Between group comparisons will include remission rate based on GAD diagnosis using the chi square test and clinically significant change which will be examined according to procedures described by Jacobson et al. [65, 66]. Change on the Sheehan Disability Scale will be analysed according to Sheehan and Sheehan’s [67] criteria. In order to determine whether the effects of the treatment are sustained over time, the post-treatment, 6 and 12-month data of the experimental group will be used. Repeated measures ANOVA will be carried out on the different variables and followed by contrast analyses. All model assumptions will be checked. Participants’ and LPs’ perception of treatment will be analyzed by calculating the frequency of each answer choice for the various statements and by summarizing comments.

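### Withdrawn participants are asked for one further assessment at an unstated time, so up to about 39 of 130 may have no observed 15-week outcome in the intention-to-treat comparison

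*Protocol article*

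**What the plan says.** **Withdrawal (Participants).** A participant is withdrawn at his or her own request, or "if an unforeseen condition prevents him or her from continuing to participate in the study or benefiting from the treatment". The rule that follows is "In the case of a withdrawal, the participant will be asked to answer the measurement instruments one last time". No time is attached to this assessment, and no later scheduled assessment is described for someone who has been withdrawn.

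**Sample size (Participants).** "In anticipation of an estimated 30% drop-out rate based on previous work [41], a total of 130 people will be admitted to the study", the aim being to end with 90, that is 45 per group.

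**Analysis (Data management and analysis).** The analysis follows intention to treat: "data from all participants included in the study will be analyzed according to the randomization scheme". The groups are compared on pre- and post-treatment data. A separate maintenance analysis uses the experimental group's post-treatment, 6-month and 12-month data. On incomplete data: "Missing data will be handled using multiple imputation".

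**Timing (Treatment; Procedure).** Treatment and the waiting period each last 15 weeks, so the comparison point is about week 15 in both arms.

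**The concern.** An intention-to-treat comparison needs each randomised person's outcome at the comparison point, however many sessions were completed. One of the grounds for withdrawal, being unable to benefit, concerns treatment rather than willingness to be measured. Yet it leads to the same single closing assessment as leaving the study altogether. The step from 90 to 130 points the same way, because drop-outs are planned as people who do not count towards the required number.

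Followed as written, these rules could leave nearly a third of the randomised sample without an observed value at the time of the main comparison. The estimate for those people would come from an imputation model whose key assumption cannot be checked in the data, namely that drop-outs' unseen week-15 scores follow from what was observed. An outcome that was not collected cannot be recovered at the analysis stage, so this has to be settled in the follow-up rules.

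**Working it through.** **1. The plan's own figures.** Drop-out step: 90 / (1 − 0.30) = 128.6, so 129. The plan's 130 agrees after rounding (130 × 0.70 = 91). The 30% is therefore treated as absent from the comparison.

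The 90 itself does not follow from its stated inputs. The plan says "Assuming an effect size of .65", with alpha .05 and power .80. Taking alpha as two-sided (the side is not stated), 2 × (1.960 + 0.842)² / 0.65² = 37.2, so 38 per arm, or 39 by the t-test. That is 76 to 78 in total. The stated 90 errs on the safe side: 45 per arm gives t-test power of about 0.86. Power among those who stay is not the problem here.

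**2. How many may lack a week-15 value.** 0.30 × 130 = 39, or about 19 to 20 per arm if allocation and drop-out are equal. At other drop-out rates: 13 at 10%, 26 at 20%, 52 at 40%. These are upper figures, since some closing assessments may fall close to week 15.

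**3. Follow-up in the experimental arm.** The maintenance analysis uses three time points. One further assessment can fill at most one of them, so a person withdrawn before post-treatment lacks at least two. This holds whatever the timing of that assessment.

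**4. Size of the possible error.** Assume 30% drop-out in each arm, with none of these people observed at week 15. In SD units:

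- true effect = 0.70 × (effect in stayers) + 0.30 × (effect in drop-outs)
- estimate = 0.70 × (effect in stayers) + 0.30 × (effect imputed for drop-outs)
- error = 0.30 × D, where D = imputed effect − true effect in drop-outs

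| D (SD) | Error (SD) |
|---|---|
| 0 | 0 |
| 0.2 | 0.30 × 0.2 = 0.06 |
| 0.4 | 0.30 × 0.4 = 0.12 |
| 0.65 | 0.30 × 0.65 = 0.195 |

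The last row is an extreme: drop-outs gain nothing but are imputed the full .65. The true effect would be 0.70 × .65 = .455 and the estimate .65. The document gives no value for D.

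**5. Direction.** D is the imputation error in improvement for experimental drop-outs minus the same error for control drop-outs. It is positive if experimental drop-outs improve less than imputed. It is negative if, for example, they leave because they are already better. Errors of the same sign in the two arms partly cancel.

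**6. What measuring everyone would do to power.** With 65 per arm, SD unchanged and two-sided alpha .05 (t-test):

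| Effect in drop-outs | Overall effect | Power |
|---|---|---|
| none | .455 | 0.73 |
| a quarter of .65 | .504 | 0.81 |
| half of .65 | .55 | 0.88 |
| full .65 | .65 | 0.96 |

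Complete follow-up would keep power at or above .80 unless drop-outs gain less than about a quarter of the assumed effect. In that case the lower figure reflects the smaller true intention-to-treat effect.

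**The case against.** The strongest reply is that the article does not say what a critic may read into it. Four points deserve an answer.

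- **Timing.** A reader might infer that withdrawn participants are measured at withdrawal and never at week 15. The text gives no time, and the schedule table and trial figure are not available here. This stands: the timing is the natural reading, not a stated rule. It does not rescue the 6- and 12-month data (step 3).
- **Stopping sessions is not said to trigger withdrawal.** Non-adherence appears to be tracked: a form records for every participant whether the protocol was followed, and lay providers log the reading and exercises completed. This stands in part. Missing sessions need not mean exit, but a ground that concerns treatment benefit still leads to withdrawal, and no continued schedule is described for those people.
- **Uneven arms.** A reader might infer that withdrawal for inability to benefit can apply only to people in treatment. The documents do not support that. The ground is an unforeseen condition, controls are due the same treatment after waiting, and they are called four times during the wait. A condition could exclude someone in either arm.
- **Imputation is planned.** The closing score could already serve as a predictor, which would bring in information from drop-outs themselves. The imputation model may properly be left to the analysis plan, and its absence is not a fault. This stands, but an earlier score still reaches week 15 only through an assumption, and better modelling cannot replace an outcome that was not collected.

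The plan also limits loss: questionnaires are completed at home on paper or online, and $20 CAD is paid for each post-treatment and follow-up assessment.

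**Conclusion.** The point holds as a weakness in the follow-up rules and should be corrected. The withdrawal rule, the allowance for drop-out and the intention-to-treat promise do not fit together. As written, up to about 39 of 130 participants may lack an observed outcome at the 15-week comparison, and withdrawn experimental participants cannot supply the full set of post-treatment and follow-up values. The 39 rests on the plan's own 30%, on drop-out occurring before week 15, and on closing assessments falling away from week 15.

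The possible error is about 0.30 × D, for instance 0.06 SD at D = 0.2 and 0.195 SD at D = 0.65. A reader might infer that the effect is bound to be overstated by about 0.20 SD. The documents do not support that. The figure is one end of a range: it requires that no drop-out has usable data, that experimental drop-outs gain nothing, that imputation ignores the closing score, and that .65 is an effect in completers, which the plan does not say. Neither the size nor the sign can be fixed from the document.

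**What to change.** In the Participants and Procedure sections:

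1. Separate stopping the sessions from leaving the study. The grounds for stopping treatment need not change; the point is what is measured afterwards.
2. In both arms, ask everyone who stops sessions or waiting-period contacts, and has not refused contact, to complete at least the PSWQ and GAD-7 at the scheduled 15-week point. In the experimental arm, ask for them at 6 and 12 months as well.
3. State when the withdrawal assessment takes place.
4. State that a score taken off schedule enters the multiple imputation as an auxiliary variable and does not stand in for the post-treatment value.

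The cost is a short amendment, slightly more follow-up work, and $20 CAD for each extra post-treatment or follow-up assessment. For 39 people at the 15-week point that is at most 39 × 20 = $780 CAD. For about 20 experimental participants at two further follow-ups it is at most 20 × 2 × 20 = $800 CAD. The questionnaires and the paper and online routes already exist. Some participants will still decline, so imputation remains necessary, but for fewer people.

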### Measures

#### Initial telephone screening

A structured interview protocol will be used by the site’s professional research assistant to conduct a partial verification of participation criteria. The presence of at least subthreshold GAD at this point will be based on the presence of various worry themes and at least moderate scores on items of the Worry and Anxiety Questionnaire (WAQ [44]) assessing anxiety and worries, somatic symptoms, and their interference during the past 6 months. The WAQ is an 11-item self-report screening questionnaire that was developed for the rapid assessment of GAD. Items measure symptoms on a 9-point Likert scale with three qualifying statements (for the lowest, middle and highest ratings on the scale).

#### Telephone clinical psychological assessment

Eligible participants will be evaluated by independent research assistants (i.e., not LPs or researchers) experienced in clinical assessment. After initial training, they will be supervised by independent clinicians (i.e., not the researchers). Following the collection of socio-demographic data (age, sex, education, marital status, main occupation, residence, income, health status and place of birth), use of medication for anxiety will be assessed with questions about type and dose of drugs used in the past 3 months. Drugs classified as anxiolytics (e.g. benzodiazepines) or antidepressants (e.g. SSRIs) will be considered. Cognitive difficulties will be assessed using the T-MMSE. A diagnostic evaluation will be conducted using the Anxiety and Related Disorders Interview Schedule for DSM-5 (ADIS-5 [45]). The ADIS-5 is a structured interview used to confirm the presence or absence of anxiety disorders and associated psychiatric diagnoses. Various measures will be put in place to ensure that the diagnostic assessment is standardized and accurate: all assessors will receive the same training in the use of ADIS-5, supervision will be mandatory for the first two assessments and every five assessments thereafter, ad hoc supervision will be available and the supervisors will be the same for all sites. Each interview will be recorded on a digital audio device to allow for the calculation of interrater agreement.

#### Primary outcome measures

These measures will evaluate the symptoms of GAD. The PSWQ will be used to measure the tendency to worry. Statements are rated on a scale ranging from 1 to 5 and a higher total score indicates a greater tendency to worry. The psychometric qualities of the PSWQ with older adults are satisfactory [46]. The GAD-7 [23] will be used to assess the severity of GAD symptoms. GAD-7 statements are answered on a scale ranging from 0 to 3 and a higher total score suggests greater severity. Wild et al. [47] have shown the validity of the GAD-7 for older adults.

#### Secondary outcome measures

Measures will be used to evaluate changes in the psychological mechanisms targeted by treatment. Items on the Intolerance to Uncertainty Inventory (IUI [48]), the Negative Problem Orientation Questionnaire (NPOQ [49]), the Cognitive Avoidance Questionnaire (CAQ [50]), and the Why Worry Questionnaire (WWQ [51]) are all rated on scales ranging from 1 to 5. Higher total scores suggest higher intolerance to uncertainty (IUI), more negative attitudes toward problems (NPOQ), more likely use of cognitive avoidance (CAQ), and greater belief that worrying is useful (WWQ), respectively. All these instruments have been validated [48–51].

The Geriatric Anxiety Inventory (GAI [52]) evaluates anxiety symptoms in general. Depressive symptoms will be evaluated with the Geriatric Depression Scale (GDS [53]). The GAI and GDS have been designed specifically for an older population and their validity and reliability is well established. A higher total score for the GAI and GDS is indicative of greater severity of symptoms. The Insomnia Severity Index (ISI [54]) assesses sleep difficulties. Each statement is rated on a scale ranging from 1 to 4. A higher total score suggests more severe insomnia. Bastien et al. [55] demonstrated the validity and sensitivity of the ISI in older adults. The degree of functional deficit in different areas of activity (e.g. family life / domestic tasks) will be assessed with the Sheehan Disability Scale (SDS [56]). The validity of the SDS has been established [57]. Secondary outcomes will also include diagnosis of GAD, as assessed by the ADIS-5, and cognitive difficulties, as assessed by the T-MMSE.

#### Other measures

The Anxiety Literacy Questionnaire (A-Lit [60]) assesses mental health literacy specific to anxiety. Items are answered with one of three options – true, false or don’t know. Higher scores indicate higher mental health literacy of anxiety. The short version of Sarason’s Social Support Questionnaire (SSQ6 [61]) measures satisfaction and availability of appraisals of social support. The Treatment Motivation Questionnaire (TMQ [62]) measures the dimensions of an individual’s motivation for entering treatment. Specifically, it contains subscales measuring external and internal motivation as well as confidence in treatment outcome and help-seeking behaviors. The version used in the present study does not include the *Help seeking* subscale. Items are listed on a 7-point Likert scale ranging from 1 (not at all true) to 7 (very true). The Credibility/Expectancy Questionnaire (CEQ [63]) evaluates how each participant views the credibility of the treatment and the possible improvements that can be achieved from the treatment. The items are listed on a 9-point Likert scale, with a higher score indicating more trust in the treatment. Finally, the Working Alliance Inventory (WAI [64]) assesses the quality of the relationship between the participant and his LP. The WAI has two versions: one for the participant and another for the LP. Items are rated on a 7-point Likert scale, with higher scores indicative of greater alliance.

### Treatment

Treatment will be the same as used in our previous study [33]. All treatment material will be sent to participants by the site’s professional research assistant. Prior to beginning treatment, the LP will contact the participant, ensure that he has received the material, briefly explain how the treatment works, tell the participant that he can start and make an appointment with him for the first telephone session. Complete treatment duration will be 15 weeks and be based on a participant’s manual consisting of eight modules. The main components of treatment are relaxation, differentiation of the main types of worries, learning to tolerate uncertainty, questioning false beliefs about worries, problem solving, cognitive exposure, and planning pleasant activities. The content of the modules is presented in Table 1. Each module will be the topic of one to three telephone sessions with the LP, at the rate of one session per week. The participant will be asked to read the corresponding module each week and do the recommended exercises. The sessions with the LP will be limited in duration (30 min maximum) and the role of the LP will be restricted to providing support within treatment procedures, namely motivational support (motivate the participant to continue treatment), emotional support (make the participant feel he is understood), and technical support (track activities done and to be done and answer technical questions related to treatment). Each session will follow an identical sequence: it will begin with a summary of the activities completed since the last session, followed by answering participant’s questions and finishing with planning the next week’s activities. LPs will not be allowed to practice psychotherapy in any form including applying techniques to modify participant’s beliefs and behaviors such as described in the treatment manual.

**Table 1 Tab1:** Content of the Modules

Module Title	Number of sessions	Content
1. Therapy goals and basic components of anxiety	1	• Therapy characteristics • Key elements for success • The two types of worries
2. Relaxation	1	• Abdominal breathing • Progressive muscle relaxation • Imagery
3. Tolerating uncertainty	3	• Exposure to uncertainty
4. Enjoying yourself	2	• The relation between anxiety and depression • Identification of pleasant activities • Planning pleasant activities
5. Correcting false beliefs	1	• Questioning false beliefs about worrying
6. Effective problem solving	3	• Steps for effective problem solving
7. In my mind … cognitive exposure	3	• Exposure to problems with uncertain outcomes
8. Relapse prevention	1	• Summary of learnt techniques • Review of gains • Relapse prevention advice

